## Abstract

**Background:** Recurrent Aphthous Stomatitis (RAS) is a common ulcerative disease of the oral mucosa which is characterized by pain, and recurrent lesions in the oral cavity. This condition is quite painful, causing difficulty in eating, speaking and swallowing. Topical medications have been used for this condition, but the obstacle in using topical medications is the difficulty of achieving drug effects due to saliva wash out. This problem can be overcome by film hydrogel formulation which can protect the ulcer and reduce the pain to some extent. α-mangostin is a xanthone isolated from the rind of the mangosteen fruit. One of the activities of α-mangostin is anti-inflammatory effects, which operate through the characteristic mechanism of inhibiting the inflammatory response. This protocol study aims to investigate the efficacy of an α-mangostin hydrogel film with a chitosan alginate base for recurrent aphthous stomatitis (RAS) in comparison with a placebo over a period of 7 days.

**Study design:** This is a two-arm, double blinding, randomized controlled trial enrolling patients with RAS. The efficacy test of α-mangostin Hydrogel Film will be tested against the placebo. Patients with RAS will be allocated randomly into the two arms and the hydrogel film will be administered for 7 days. The diameter of ulcer and visual analog scale (VAS) score will be used as the primary efficacy endpoint. The outcome measure will be compared between the two arms at the baseline, day 3, day 5, and at the end of 7 days.

**Discussion:** The purpose of this clinical research is to provide scientific evidence on the efficacy of α-mangostin hydrogel film with a chitosan alginate basis in treating recurrent aphthous stomatitis. The trial is expected to improve our capacity to scientifically confirm the anti-inflammatory effectiveness of α-mangostin compounds in a final formulation that is ready to use.

**Trial registration:** NCT06039774 (14 September 2023).

## 1 Background

Recurrent Aphthous Stomatitis (RAS) is a common ulcerative condition affecting the oral mucosa, characterized by recurrent painful lesions in the oral cavity. This condition can significantly impact an individual’s quality of life, causing difficulties in eating, speaking, and swallowing. The etiology of RAS is not fully understood, despite numerous clinical observations and research efforts. Several factors are believed to contribute to the development of RAS, including genetic predisposition, mechanical trauma, deficiencies in micronutrients and vitamin B_12_, increased oxidative stress, food allergies, microbial factors or infections, anxiety, internal disorders, hormonal imbalances, and systemic disorders that are associated with lesions clinically similar to RAS like anemias, HIV infection, and reactive arthritis (Tarakji et al., 2015; Sharma and R, 2018; Rivera, 2019).

A cross-sectional study conducted in Shanghai, China reported that among the study population, 10.8% (11,054 individuals) were found to have oral mucosal lesions, and within this group, 1.48% suffered from RAS (Feng et al., 2015). In contrast, a separate cross-sectional study involving 4,255 North Indian individuals found an overall prevalence of RAS to be 18.93% (Kaur et al., 2021). Notably, the prevalence of RAS in the general population varies between 5% and 25% in different categories (Ślebioda, Szponar and Kowalska, 2014). It is important to mention that there is no universally standardized treatment for RAS; however, the primary objectives of all treatments are to alleviate ulcer pain, promote ulcer healing, and prevent recurrence (Sánchez-Bernal et al., 2020).

Topical medications represent the primary approach to treating RAS due to their cost-effectiveness and safety. These medications come in various forms, including liquid, solid, and semisolid preparations, such as mouthwashes, aerosols, lozenges, and ointments (Sharma et al., 2022). However, a significant challenge in using topical drugs is the limited effectiveness in achieving the desired therapeutic effects. This limitation is primarily attributed to the phenomenon of “salivary washout,” which leads to the removal and flushing of the drug from the mucosal surface. To address this issue, numerous studies have focused on enhancing the duration of drug contact with the oral mucosa. The advancement of drug delivery systems for RAS treatment is driven by three keys objectives: prolonging the residence time of the therapy at the ulcer site, delivering adequate drug concentrations to the ulcer, and alleviating pain. A promising solution entails the utilization of film formulations that act as a protective barrier for the ulcer, shielding it from external stimuli and offering relief from pain (Suharyani et al., 2021).

An oral mucoadhesive film containing chitosan was evaluated in a double-blind, randomized controlled clinical study. The findings revealed its efficacy in significantly expediting the healing process and alleviating pain in individuals afflicted with RAS. Chitosan, owing to its mucoadhesive properties, drug release characteristics, and pharmacodynamic effects, exhibits substantial potential as a drug delivery agent for the treatment of RAS (Shao and Zhou, 2020).

Herbal medicine offers an alternative approach for treating RAS by reducing pain, accelerating the healing process, and promoting overall recovery (Rezvaninejad et al., 2017). In traditional Indonesian medicine, the rind of the mangostin fruit (*Garcinia mangostana* L.) has been utilized for its therapeutic properties. α-mangostin, an xanthone compound derived from the mangosteen fruit’s rind, has been used in traditional medicine. One of its notable activities is its anti-inflammatory effect, achieved through the mechanism of inhibiting of NO, IL-1β, TNF-α, NF-κB and selective COX-2 along with blocking iNOS (Chavan and Muth, 2021). This property makes α-mangostin a promising compound for potential use in RAS management. To facilitate the delivery of α-mangostin, a combination of two mucoadhesive polymers, namely, sodium alginate and chitosan, has been employed as a drug delivery system (Mohan et al., 2018; Wathoni et al., 2019).

In a prior study, the development and assessment of α-mangostin hydrogel films with a chitosan-alginate base for *in vivo* therapy of RAS were conducted using white Wistar rats as test subjects. The results showed a remarkable 93% healing rate within 7 days (Milanda et al., 2022). As a result, further investigations will be carried out to evaluate the clinical efficacy and safety of the chitosan-alginate-based α-mangostin hydrogel film in RAS patients. This research aims to assess the suitability of the finished product for practical use in RAS treatment.

## 2 Methods

### 2.1 Study design

This is a two-arm, double-blinded, randomized controlled trial scheduled to take place at the Padjadjaran University Dental and Oral Hospital in Bandung, Indonesia. The trial aims to evaluate the efficacy and safety of α-mangostin hydrogel film in comparison to a placebo. Patients diagnosed with RAS will be randomly assigned to one of the two arms, and they will receive the mucoadhesive film for a duration of 7 days. The primary efficacy endpoints will be determined based on the measurement of ulcer diameter and the use of the Visual Analog Scale (VAS) score. These outcome measures will be assessed at various time points, including prior to the initial visit (baseline), on day 3, day 5, and at the conclusion of the 7-day treatment period based on previous trial on 2020 and 2022 (Ghorbani et al., 2020; Molania et al., 2022).

Ethics approval has been obtained from Research Ethics Committee of the Faculty of Medicine, Universitas Padjadjaran, Indonesia (approval reference number: 806/UN6.KEP/EC/2023). The trial was registered in the Clinicaltrials.gov registry (Trial number NCT06039774).

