### 2.5 Sample size

Sample size was calculated with the lemeshow formula. Calculations were performed using 80% power, a 5% significance level, and 20% dropout rate. The required sample size was approximately 19 subjects for each group. We plan to enroll 24 subjects in each group to allow for a 20% withdrawal rate.

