### 2.9 Statistical analysis

All data will be analyzed using the Independent Samples *t*-test model in SPSS Version 26 to compare age, time of new ulcer eruption, pain scores (VAS), and ulcer size. The Chi-Square test will be employed to compare gender distribution, distribution of RAS on mucosal epithelium, history of drug allergies, and dietary habits. The significance level for statistical tests was set at α = 0.05, with a confidence level of 80% (Ghorbani et al., 2020; Shao and Zhou, 2020).

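### Two primary measures, three post-baseline comparison days and α = 0.05 for the tests, with no primary day and no either/both rule: the 5% level is not secured

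*Protocol article*

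**What the plan says.** The places that bear on this point, all in the protocol article, are these.

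- **Primary measures.** Section 2.1 uses the plural: "The primary efficacy endpoints will be determined based on the measurement of ulcer diameter and the use of the Visual Analog Scale (VAS) score". The Abstract names the same two measures but uses the singular: "The diameter of ulcer and visual analog scale (VAS) score will be used as the primary efficacy endpoint".
- **Days.** The Abstract describes between-arm comparisons by day: "The outcome measure will be compared between the two arms at the baseline, day 3, day 5, and at the end of 7 days". Section 2.1 lists baseline and then the same days as assessment times ("on day 3, day 5, and at the conclusion of the 7-day treatment period"). Neither singles out a day.
- **Test and level.** Section 2.9 states: "All data will be analyzed using the Independent Samples *t*-test model in SPSS Version 26", and lists VAS pain and ulcer size among the variables. It adds: "The significance level for statistical tests was set at α = 0.05". It mentions no order of testing and no split of α.
- **Sample size.** Section 2.5 states: "Calculations were performed using 80% power, a 5% significance level, and 20% dropout rate". It gives 19 evaluable and 24 enrolled per group, and ties these to neither measure and to no day.

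**The concern.** Read together, these statements allow two measures × three post-baseline days = six between-arm t-tests of primary measures, each at 0.05. VAS is also recorded daily (sections 2.7 and 2.8), so six is not the largest possible count.

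The 5% in sections 2.5 and 2.9 is the error rate of one test. Whether it is also the error rate of the trial's efficacy conclusion depends on a success rule, and the article gives none. With about 19 evaluable patients per arm, a lone p < 0.05 for one measure on one day could not be told apart from selection among several tests. The trial's main conclusion rests on this.

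**Working it through.** **Inputs from the article:** two primary measures (section 2.1, Abstract); post-baseline days 3, 5 and 7 (Abstract); independent-samples t-test at α = 0.05 (section 2.9); 80% power, 5% level, 20% dropout, 19 evaluable and 24 enrolled per arm (section 2.5).

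**Assumptions, not in the article:** two-sided tests; correlation between days from 0 to 0.9; correlation between the two measures from 0 to 0.7; normal data.

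**Step 1. The plan's own figures.** 19 / (1 − 0.20) = 23.75, rounded up to 24, so the enrolment figure reproduces. The 19 cannot be checked, because no effect size or SD is given. Under the normal approximation it corresponds to a standardised difference of (1.960 + 0.842) × √(2/19) = 0.909.

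**Step 2. Independent tests.**
- Any of six, either direction: 1 − 0.95^6 = 26.5%.
- Any of six, favouring the film: 1 − 0.975^6 = 14.1%.
- One named day, either of two measures: 1 − 0.95² = 9.75%.
- Both measures, each on any day: (1 − 0.95³)² = 0.1426² = 2.0%.

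**Step 3. Correlated tests.** Simulation under no effect, 19 per arm, six two-sample t-tests at two-sided 0.05, 40,000 to 60,000 replicates per setting. The table assumes equal correlation between days.

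| Between-day r | Between-measure r | Any of six, two-sided | Any of six, favouring film | Day 7 only, either measure, two-sided | Both measures, each on any day |
|---|---|---|---|---|---|
| 0.3 | 0.3 | 24.9% | 12.5% | 9.4% | 2.4% |
| 0.5 | 0.5 | 22.1% | 11.1% | 9.1% | 3.3% |
| 0.7 | 0.5 | 19.4% | 9.7% | 9.1% | 2.5% |
| 0.8 | 0.5 | 17.3% | 8.9% | 9.1% | 2.2% |
| 0.9 | 0.7 | 13.6% | 6.7% | 8.2% | 3.0% |

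Over all settings tried, including correlations that decay with time for the first three quantities, the ranges are about 14-26%, 7-14%, 8-10% and 1-5%. One measure alone over the three days gives about 8-14%.

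**Step 4. Power if α is split.** At 0.909 SD with 19 per arm, the noncentrality is 0.909 × √(19/2) = 2.80.
- At α = 0.05: Φ(2.80 − 1.960) = 80%.
- At α = 0.025: Φ(2.80 − 2.241) = 71%.
- For 80% power at α = 0.025: 2 × (2.241 + 0.842)² / 0.909² = 23.0, just above 23, so 24 evaluable per arm. With 20% withdrawal, 24 / 0.80 = 30 enrolled per arm.
- Bonferroni over all six tests (0.05/6 = 0.00833) would need 30 evaluable per arm.

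**The case against.** A reader might infer that the plan fixes six primary tests, any one of which proves efficacy, and so carries a false-efficacy rate of roughly a quarter. The documents do not support this, for four reasons.

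- **No success rule is stated.** The Abstract joins the two measures with *and* and treats them as one endpoint, so a both-required reading is not excluded. Under it the error is at or below about 5%. That reading sits uneasily with the sample size, since two measures at 80% power each give joint power of 0.8 × 0.8 = 64% if independent, but the text does not rule it out.
- **The count of six is assembled from several places.** Section 2.1 speaks of assessment, and section 2.9 names the t-test without days. Only the Abstract says the arms are compared day by day.
- **The correlations are assumed.** The figure moves from 26.5% down to about 14% across plausible values.
- **The larger figures count both directions.** A false result in favour of the film is about half as frequent.

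All four points stand, and they make the size conditional.

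It can also be said that a multiplicity adjustment belongs in a statistical analysis plan, which is not shown, and that a journal article is condensed. That is fair as to an unstated adjustment, which is not the point here. The article does state two primary measures, several comparison days, the test and the level. An analysis plan that controls the error would still have to be reconciled with that text.

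**Conclusion.** The point holds in conditional form. What the article fixes does not secure the 5% level, because it gives two primary measures and several comparison days at 0.05 without a primary day or an either/both rule.

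The size depends on the missing rule:
- Either measure on any of the three days: about 14-26% two-sided, or about 7-14% favouring the film against 2.5% for one test.
- Either measure on one named day: about 8-10% two-sided.
- Both measures required: at or below about 5%, so no material inflation.

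These figures assume two-sided t-tests, 19 evaluable per arm and the correlations stated above. That the protocol must state its rule depends on none of these figures. An unconditional error rate for the plan cannot be given.

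**What to change.** Before unblinding, amend sections 2.1 and 2.9, and align the Abstract and the analysis plan with them.

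1. Name one primary contrast at two-sided 0.05: one measure at one pre-named day, or its average over days 3, 5 and 7 from a single repeated-measures model.
2. Test the same contrast for the other measure at 0.05 only if the first is significant.
3. Report the day-specific comparisons as supportive, with no claim attached.

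**Cost.** Wording only, with no extra patients; section 4 says recruitment is ongoing. It does change the stated status of one primary measure, so it is a protocol amendment and not just an analysis-plan edit. Which measure comes first is the sponsor's choice. If the first fails, there is no claim on the second. Because section 2.5 names no endpoint, the power for the chosen contrast should be stated at the same time.

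**If either measure alone should support a claim**, use Holm across the two, on one pre-named contrast each, and restate the power. At the first Holm step (0.025), a measure with the implied effect of 0.91 SD has about 71% power with 19 evaluable per arm. Restoring 80% at that level takes 24 evaluable, or 30 enrolled, per arm. The 71% is the figure when the other measure shows no effect; it is higher when both respond, since Holm then tests the second at 0.05.

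**If both measures are meant to be required**, say so, name the day, and restate the joint power.

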### 2.2 Study setting

The research will take place at the Padjadjaran University Dental and Oral Hospital, located in Bandung, Indonesia. Study participants will be selected from among patients diagnosed with Recurrent RAS who seek care at the oral medicine polyclinic of Padjadjaran University Dental and Oral Hospital.

### 2.3 Participants recruitment

The participants for this research project will be drawn from a pool of patients at the Padjadjaran University Dental and Oral Hospital who have been diagnosed with RAS by oral medicine specialist dentist. The participation in this study is entirely voluntary. The recruitment of patients will involve a screening process to assess their eligibility, taking into consideration the inclusion and exclusion criteria. Patient who are eligible and interested in participating in this clinical study will be provided with a detailed written informed consent and verbal explanation of the study procedures and will be randomly allocated to either the α-mangostin hydrogel film group or the placebo film group.

### 2.4 Inclusion and exclusion criteria

The efficacy test inclusion criteria include: participants aged between 18 and 59 years at the time of enrollment; patients who have been diagnosed with minor RAS from a dentist and are capable of adhering to the research protocol and providing informed consent. Eligible participants are those presenting with a minor RAS ulcer diagnosed by a dentist within 48 h of its initial appearance and who have refrained from using any medications for RAS ulcer treatment. Exclusion criteria involve individuals concurrently participating in other ongoing clinical trials.

The efficacy test exclusion criteria include: individuals with herpetiform ulcers or major aphthous ulcers; subjects with ulcers associated with systemic diseases, such as Behcet’s disease or Crohn’s disease; participants diagnosed with other severe medical conditions, including arrhythmia, uncontrolled hypertension, diabetes, hepatitis, and kidney failure; pregnant or breastfeeding women, as well as women planning to conceive during the study period. Individuals with suboptimal oral hygiene that necessitates treatment; patients with chronic illnesses requiring treatment involving antibiotics, hormones, nonsteroidal anti-inflammatory drugs, immunosuppressants, immunoenhancers, cytotoxic drugs, or cell cycle agents known to impact the oral mucosa; subjects with mental health disorders or limited cognitive capacity.

### 2.5 Sample size

Sample size was calculated with the lemeshow formula. Calculations were performed using 80% power, a 5% significance level, and 20% dropout rate. The required sample size was approximately 19 subjects for each group. We plan to enroll 24 subjects in each group to allow for a 20% withdrawal rate.

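### The single 80% power and 5% significance statement describes one test, but the protocol has two primary endpoints, each tested at an unadjusted 0.05 with no success rule

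*Protocol article*

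**What the plan says.** Two endpoints are primary. The abstract says "The diameter of ulcer and visual analog scale (VAS) score will be used as the primary efficacy endpoint", and section 2.1 has it in the plural: "The primary efficacy endpoints will be determined based on the measurement of ulcer diameter and the use of the Visual Analog Scale (VAS) score". Neither place ranks the two, names a deciding day among days 3, 5 and 7, or says whether success needs one endpoint or both.

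Section 2.5 contains one sample-size statement. The method is given as "Sample size was calculated with the lemeshow formula", the design values as "Calculations were performed using 80% power, a 5% significance level, and 20% dropout rate", and the result as "The required sample size was approximately 19 subjects for each group". Enrolment follows: "We plan to enroll 24 subjects in each group to allow for a 20% withdrawal rate". The section gives no endpoint, day, difference or SD.

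Section 2.9 covers both endpoints with one test: "All data will be analyzed using the Independent Samples *t*-test model in SPSS Version 26". The level is common to all tests: "The significance level for statistical tests was set at α = 0.05". It mentions no split or ordering.

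**The concern.** A sample size for two means, with one power and one significance level, is a statement about one comparison. Here it stands alone above two primary comparisons, so a reader will take 80% power at 5% error as a property of the trial's primary question. Whether that is true depends on a success rule that the article does not state. The two natural rules break different halves of the statement: either-wins breaks the 5%, and both-needed breaks the 80%.

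At stake is how the result is read. One significant endpoint out of two could be reported as a positive trial at 5% error when the error was higher. Or a trial that misses on one endpoint could be read as having had 80% power for the pair. If the rule is chosen after unblinding, neither reading can be defended.

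**Working it through.** **Inputs from the protocol article.** 19 evaluable and 24 enrolled per group, 80% power, 5% significance, 20% dropout (section 2.5). Two primary endpoints (abstract, section 2.1). Independent-samples t-test for each at 0.05 (section 2.9).

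**Assumptions, not in the article.** Two-sided tests, one day per endpoint, exactly 19 evaluable per group, the same standardised effect d on both endpoints (relaxed in step 5), and a correlation ρ of 0 to 0.9 between the two test statistics.

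**1. The plan's own figures.** 19 / (1 − 0.20) = 23.75, rounded up to 24, so the dropout step is correct. The 19 cannot be reproduced forward, because section 2.5 gives no difference or SD.

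**2. Effect implied by 19 per group for one test.**
- Normal approximation: d = (1.960 + 0.842) × √(2/19) = 2.8016 × 0.3244 = 0.909.
- Exact t-test (36 df, noncentrality d√(19/2)): 80% power at d = 0.934. At d = 0.909 the t-test has 77.8%.

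Both values are carried forward, because the article does not show which form of the formula was used.

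**3. Either endpoint suffices, each at 0.05.** Family-wise error for two independent tests is 1 − 0.95² = 0.0975. With positive correlation it is 1 − P(|Z₁| < 1.96, |Z₂| < 1.96), which is 9.5% at ρ = 0.3 and 7.0% at ρ = 0.9. It stays above 5% unless the tests are perfectly correlated. With power p per endpoint, the power to win at least one is 2p − P(both).

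**4. Both endpoints must succeed, each at 0.05.** P(both) = Φ₂(z_p, z_p; ρ), where Φ₂ is the bivariate normal distribution function and z_p the normal quantile of p.

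| ρ | Both, p = 77.8% | Both, p = 80% | At least one, p = 77.8% | At least one, p = 80% |
|---|---|---|---|---|
| 0 | 60.6% | 64.0% | 95.1% | 96.0% |
| 0.3 | 63.5% | 66.6% | 92.2% | 93.4% |
| 0.5 | 65.8% | 68.7% | 89.9% | 91.3% |
| 0.7 | 68.5% | 71.3% | 87.1% | 88.7% |
| 0.9 | 72.5% | 75.0% | 83.1% | 85.0% |

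A simulation of 100,000 trials with two correlated t-tests, run for ρ from 0 to 0.8, agreed with the joint figures to within about half a percentage point.

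**5. Unequal effects.** Joint power cannot exceed the power of the weaker endpoint. If the endpoint used for sizing has 80% and the other has d = 1.3 (t-test power 97.4%), joint power runs from 0.80 × 0.974 = 77.9% at ρ = 0 to just under 80%.

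**6. Splitting α, 0.025 each (not in the article).** Power per endpoint is 67.8% (d = 0.909) or 70.4% (d = 0.934). Power to win at least one is 91.3% (d = 0.934, ρ = 0) down to 74.2% (d = 0.909, ρ = 0.9), and mostly above 80%.

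**The case against.** **The trial need not be underpowered.** A reader might infer that the design delivers only some 60-70% power. The article does not support that as a general statement. With no split stated, a win on either endpoint at 0.05 is a possible reading, and its power is 83-96% in the table. The fault there is type I error. The 68-70% under a split is also power per endpoint, and a split usually goes with a win on either one. This objection stands, so the finding is a mismatch and not a proven shortfall.

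**Nineteen per group can give 80% for more than one endpoint.** It does so for every endpoint whose standardised effect is at least about 0.93. If the sizing used the smaller effect, both endpoints have at least 80% and joint power approaches 80%. This is also right, and it is why the joint figures are illustrative. It does not make the statement true for the pair, since joint power still does not reach 80% when the sizing endpoint has 80%.

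**More than 19 may be evaluable.** With all 24 per group evaluable at d = 0.909, joint power is about 78-85% for ρ from 0 to 0.9 (normal approximation). But section 2.5 makes its claim for 19, with the other five as a dropout allowance.

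**The 77.8% is not an error in the plan.** It rests on a guess at the formula, and the 19 is itself stated as approximate.

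**This is a condensed article.** The full protocol and analysis plan are not shown and may hold the sizing inputs and a multiplicity rule, so their absence here is no finding. What stands is internal to the text shown: it names two primaries, gives one power figure tied to neither, and sets 0.05 for the tests. A later success rule would not by itself make the 80% and 5% apply to both endpoints together.

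**Conclusion.** The point holds in a limited form. As written, the 80% power and 5% significance describe a single test and not the pair of primary endpoints. Under either-wins, power is above 80% but the family-wise error is up to 9.75%. Under both-needed, joint power is below 80%.

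The 9.75% needs only the stated α and independence of two tests. The 60-75% joint range rests on all the assumptions listed in the working, above all equal effects and 19 evaluable, and none of these is a document figure. With a clearly larger effect on the second endpoint the joint shortfall nearly vanishes. The dropout arithmetic is correct, and nothing here shows that 24 per group is too few for one named primary endpoint.

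**What to change.** Amend sections 2.5 and 2.9 together, and make the abstract and section 2.1 agree. Recruitment is under way (section 4), so do this before unblinding.

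- **Section 2.5:** tie the 80% power and 5% level to one named primary endpoint at one named day. Give the difference and SD that the investigators actually used. Do not insert 0.91 or 0.93, which are back-solved from the sample size and are not design assumptions.
- **Section 2.9:** test that endpoint first at 0.05, and test the other at 0.05 only if the first is significant. This fixed sequence holds the family-wise error for the pair at 5% without splitting α.
- **Section 2.5:** state that the 80% does not apply to success on both endpoints. Label any joint-power figure as an assumption, with its effect sizes and correlation.
- **Enrolment:** keep 24 per group.

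No patients or visits are added. The cost is that the second endpoint can be claimed only if the first succeeds, and that the protocol openly claims 80% power for one endpoint only.
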